### **8. Avoiding Risk of SARS-CoV-2 Transmission**

To avoid the risk of SARS-CoV-2 transmission in connection with this trial, the following strategies will be adopted:

- Participants will be recruited only from government approved isolation and treatment centres which have been specially provisioned to safely care for COVID-19 patients and restrict contact with uninfected individuals.
- All procedures involving specimen collection, processing and analysis will be carried out in appropriately equipped facilities by staff trained in the relevant technical and safety procedures and in line with national/international guidelines on personal protective equipment and laboratory biosafety.
- Study personnel will wear personal protection equipment (PPE) at all times during any necessary physical interactions. Both participants and study personnel will be instructed to adhere to national and regional guidance for COVID-19-related safety measures.
- To further limit exposure, daily vital signs and symptoms will be self-monitored by participants whenever possible.

## 9. Specimen Collection for SARS-CoV-2 Viral Load

Saliva will be self-collected by participants under supervision into 15 mL screw-cap tubes from which 1.5-2mL will be transferred into 2 mL cryo vials for SARS-CoV-2 viral load determination. Where necessary nasopharyngeal swab specimen will be collected using Dacron® or Copan® polyester flocked swabs. Insert flexible wire shaft minitip swab through the nares parallel to the palate (not upwards) until resistance is encountered or the distance is equivalent to that from the ear to the nostril of the patient, indicating contact with the nasopharynx. Swab will reach a depth equal to distance from nostrils to outer opening of the ear and gently rubbed and rolled. Swab will be left in place for at least 15 seconds to absorb secretions and then slowly removed while being rotated.

## 10. Specimen Shipment and Storage

Samples will be stored at 4°C for analysis within 24 hours after collection. If a delay in testing or shipping is expected, specimens will be stored at -70°C or lower. Each swab will be placed in sterile tube containing 2-3 mL of VTM containing antifungal and antibiotic supplements. Repeated freezing and thawing of specimens will be avoided. Sterile saline will be used in the absence of VTM if samples will be stored at -70°C and analysed within 72 hours. Specimens will be packaged, shipped, and transported according to the current edition of the International Air Transport Association (IATA) Dangerous Goods Regulations .

## 11. SARS-CoV-2 Detection and Viral Load Assay

Handling of COVID-19 swab specimen for molecular testing will only be carried out in Nigerian Centre for Disease Control (NCDC) accredited BSL-2 or equivalent facilities. SARS-CoV-2 detection and viral load assays will be conducted at the African Centre of Excellence for Genomics of Infectious Diseases (ACEGID), Redeemer's University, Ede, Osun State Nigeria. SARS-CoV-2 RNA will be extracted using QIAamp Viral RNA Mini Kit based on the manufacturer protocol (QIAGEN, 2020). Approximately 60µL of RNA template will be extracted from 140µL of the specimen. One-step quantitative reverse transcriptase polymerase chain reaction (q RT-PCR) technique with fluorescent probes will be used for the molecular diagnosis and quantification of SAR-CoV 2. The protocol to be used will be based on the methodology of DAAN Gene extraction kit (Anon, 2020). Briefly, 5µL of the RNA template, negative control (NC) and positive control (PC) will be analysed in a total reaction volume of 25µL. The reaction mixture in the 96 well plate tubes will be tightly covered, vortex gently, centrifuged at 8,000 rpm for several seconds and amplified based on the manufacturer reaction condition as stated below.

| Step | Cycles | Target Temperature | Running time |
|------|--------|--------------------|--------------|
| 1    | 1      | 50°C               | 15 min       |
| 2    | 1      | 95°C               | 15 min       |
| 3    | 45     | 94°C               | 15 sec       |
|      |        | 55°C               | 45 sec       |

The cycle threshold values of rRT-PCR will be used as indicators of the copy number of SARS-CoV-2 RNA in specimens with lower cycle threshold values corresponding to higher viral copy numbers. A cycle threshold value less than 40 is interpreted as positive for SARS-CoV-2 RNA. SARS-CoV-2 viral load in sputum and/or swab specimens will be determined as previously described.

## 12. Statistical Considerations

Proportion of participants with SARS-CoV-2 PCR negative result at days 7, 14 and 28 will be compared between the intervention and control groups. Analysis of clinical improvement based on the 10-category ordinal scale will be performed using time-to-event data (patients will be censored at 28-days of follow-up). Categorical variables will be analysed using the log-rank test and continuous variables will be assessed using a univariable Cox proportional hazard regression analysis. Analysis of cumulative improvement rate will be presented by Kaplan-Meier survival curves when independent variables are dichotomous or categorical. A univariable Cox regression analysis will be conducted and covariates with a  $p < 0.25$  in the univariable analysis will be included in the multivariable model. These analyses will be conducted using Stata®.

An interim analysis of data from the Pilot Stage will be conducted after the first 30 participants have completed days 1-14 of the study period. These data will provide valuable insights regarding the design, conduct and analysis of the Pivotal Stage, including sample size estimate, intervention-responsive definition of the primary and secondary endpoints, and procedures to enhance quality of trial conduct. The Trial Steering Committee will make timely recommendations for finalizing the design of the Pivotal Stage based on data from the Pilot Stage. To preserve the integrity of the Pivotal Stage, data from the Pilot Stage would only be included in the primary analyses of the Pivotal Stage data only if those using the Pilot Stage data to enlighten decisions about finalizing the design of the Pivotal Stage do not have access to information from the Pilot Stage that would be directly or indirectly informative about the efficacy and safety of the experimental regimens being evaluated in the Pivotal Stage.

## 13. Assessments of Nitazoxanide Pharmacokinetics

Following oral administration of 500 mg of nitazoxanide every 12 hours for 7 consecutive days in adults, the mean (SD)  $C_{max}$  of tizoxanide was 10.6 (2.1)  $\mu\text{g/mL}$  and no significant accumulation of nitazoxanide metabolites tizoxanide or tizoxanide glucuronide was detected. In a study that investigated nitazoxanide efficacy for pulmonary tuberculosis, a 1000 mg twice daily dose for 14 days was employed and no grade 4 or 5 adverse event was observed. The  $C_{max}$  of tizoxanide on days 5 and 14 were 11.3 (4.6)  $\mu\text{g/mL}$  and 9.0 (4.1)  $\mu\text{g/mL}$ , respectively. Therefore, to characterise the exposure-response relationship of tizoxanide when 1000 mg nitazoxanide is taken two times daily in combination with 300/100 mg atazanavir/ritonavir, pharmacokinetic (PK) sampling will be performed in trial participants on days 5 and 14 (intensive) and on days 3, 7, 10, 21, and 28 (sparse) based on the following schedule:

| Specimen               | Intensive pharmacokinetic (PK) sampling (n = 12)                                                | Sparse PK sampling (n = 49)                                                                                                                                                                    |
|------------------------|-------------------------------------------------------------------------------------------------------------|------------------------------------------------------------------------------------------------------------------------------------------------------------------------------------------------|
| Dried Blood Spot (DBS) | 0.5, 1, 2, 4, 6, 8 and 12 hours after dose on day 5
0.5, 1, 2, 4, 6, 8 and 12 hours after dose on day 14 | 12 hours after dose on day 2
12 hours after dose on day 4
12 hours after dose on day 6
12 hours after dose on day 7
12 hours after dose on day 14
12 hours after dose on day 28 |
| Saliva                 | 0.5, 1, 2, 4, 6, 8 and 12 hours after dose on day 5
0.5, 1, 2, 4, 6, 8 and 12 hours after dose on day 14 | 12 hours after dose on day 2
12 hours after dose on day 7
12 hours after dose on day 14                                                                                                  |

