### **3.4. Follow-up**

The treatment duration for participants in the intervention group will be 14 days. However, follow up will continue until day 28 after study entry at the end of which all participants will exit the study. The schedule of activities during the follow up period is presented in Table 1. Participants who stop study product should continue study participation off study product with continued evaluations as per the schedule of activities. The reason for study product discontinuation should be recorded. Daily survey, vital signs and SpO2 as well as Flu-PRO questionnaire will be recorded by participant (both on paper and cloud-based forms using their mobile device while connected to the internet). SpO2 will be measured after at least 5 minutes resting in a sitting or supine position. Participants with an SpO2 below 93% will repeat the assessment 2 hours later. If the repeat assessment is still below 93%, study clinician will be alerted.

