| Entry vital signs                                     | X     |       |       |       |          |       |          |        |            |        |        |        |
| Eligibility confirmation                              | X     |       |       |       |          |       |          |        |            |        |        |        |
| Enrolment                                             | X     |       |       |       |          |       |          |        |            |        |        |        |
| Safety blood (10 mL)                      | X     |       |       |       |          | X     |          |        |            | X      |        |        |
| Dispense standard of care                             | X     |       |       |       |          |       |          |        |            |        |        |        |
| Randomisation                                         | X     |       |       |       |          |       |          |        |            |        |        |        |
| Dispense trial intervention (BID for 14 days)         |       | X     | X     | X     | X        | X     | X        | X      | X          | X      |        |        |
| Daily vitals, including SpO 2              |       | X     | X     | X     | X        | X     | X        | X      | X          | X      | X      | X      |
| Flu-PRO                                               |       | X     | X     | X     | X        | X     | X        | X      | X          | X      | X      | X      |
| Clinical improvement assessment                       |       | X     | X     | X     | XXX      | X     | XX       | X      | XXX        | X      | X      | X      |
| Saliva or swab collection for SARS-CoV-2  | X     |       | X     |       | X        | X     |          |        |            | X      |        | X      |
| Pharmacokinetic sampling                  |       |       | X     |       | XXX      | X     |          |        |            | XX     |        |        |
| Adverse event monitoring                              |       | X     | X     | X     | X        | X     | X        | X      | X          | X      | X      | X      |
| Study exit assessment                                 |       |       |       |       |          |       |          |        |            |        |        | X      |

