 10 mL blood draws each at baseline, day 7 and day 14 will be used to assess essential biochemical (including AST, ALT) and haematology (including XXX) safety parameters.

 Sampling schedule for SARS-CoV-2 viral load: Days 0, 2, 4, 6, 7, 14, and 28.

 Sparse PK sampling in all patients paired with saliva sample for SARS-CoV-2 viral load, as well as intensive PK sampling on days 5 and 14 in 12 selected participants.

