#### 15. Protocol Amendment

The trial protocol has been designed to meet highest level of standard that will primarily ensure safety of participants and output of good and reliable data. However, major and minor modifications can sometimes be made to remove or avoid any unanticipated risk or harm to the participant or affect the integrity of study outcomes. Whenever this happens, the amendments will be saved in a new version of the protocol, with the changes from previous version highlighted in the version history page. The amended protocol will be shared with all investigators. The revised and previously approved versions of the protocol will be submitted to the ethics committees (NHREC, Nigeria and the University of Liverpool Health and Life Sciences) and NAFDAC for approval before the changes are implemented in the trial.

 Both intensive and sparse PK sampling will be performed after the morning dose of 1000 mg nitazoxanide. This will also capture the C12 and Ctrough of atazanavir/ritonavir which will be taken with the evening dose of 1000 mg nitazoxanide.

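### The sparse PK days differ between the Section 13 text, its table and Table 1, and the Day 21 and Day 28 entries have no dose to be timed from

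*Protocol*

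**What the plan says.** The protocol describes PK sampling in four places.

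- **Section 13, text.** Intensive sampling is on days 5 and 14; sparse sampling is "on days 3, 7, 10, 21, and 28 (sparse) based on the following schedule".
- **Section 13, table.** Sparse blood spots (n = 49) are at 12 hours on days 2, 4, 6, 7 and 14, plus "12 hours after dose on day 28". Saliva as a PK specimen is at 12 hours on days 2, 7 and 14. Twelve participants have intensive sampling: "0.5, 1, 2, 4, 6, 8 and 12 hours after dose on day 5", and the same times on day 14, in blood spots and saliva.
- **Footnote 5 to that table.** "Both intensive and sparse PK sampling will be performed after the morning dose of 1000 mg nitazoxanide", with the added claim that this captures both the 12-hour level and the trough of atazanavir/ritonavir, which is taken in the evening.
- **Section 4, Table 1.** PK is marked on Day 2, three times in Days 4-6, on Day 7 and twice on Day 14. Days 3, 10, 21 and 28 are blank. Footnote 3 reads: "Sparse PK sampling in all patients paired with saliva sample for SARS-CoV-2 viral load". Footnote 2 puts viral-load samples on days 0, 2, 4, 6, 7, 14 and 28.

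On dosing, Section 3.4 states: "The treatment duration for participants in the intervention group will be 14 days". Table 1 shows study drug dispensed on Days 1 to 14. Section 3.2.1 gives nitazoxanide at 8 am and 8 pm and atazanavir/ritonavir at 8 pm.

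**The concern.** The sentence that introduces the PK schedule contradicts that schedule. With four sites, some staff may work from the sentence and others from the table. Section 13 says the samples serve a tizoxanide exposure-response analysis, and footnote 3 ties sparse PK to the viral-load samples. The days therefore have to coincide with viral-load days if concentration and response are to be compared at the same visit.

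Two entries also cannot be carried out as written, because participants take no study drug on Day 21 or Day 28. Footnote 3, read literally, sends sparse PK sampling to control patients, who receive no study drug, and to Day 0, before the first dose. Footnote 5 promises a quantity that the sparse schedule does not yield.

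**Working it through.** The plan gives no derived figure to reproduce. The check compares lists of days and clock times.

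**1. Days side by side**

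| Source | Sparse days | With intensive days 5 and 14 |
|---|---|---|
| Section 13 text | 3, 7, 10, 21, 28 | 3, 5, 7, 10, 14, 21, 28 |
| Section 13 table (blood spots) | 2, 4, 6, 7, 14, 28 | 2, 4, 5, 6, 7, 14, 28 |
| Table 1 | not separated | 2, 4, 5, 6, 7, 14 |

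The Table 1 row reads the three marks in Days 4-6 as days 4, 5 and 6, and the two marks on Day 14 as one sparse and one intensive session.

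- Text and Section 13 table share days 7 and 28, out of 9 distinct sparse days (2, 3, 4, 6, 7, 10, 14, 21, 28).
- Text and Table 1 share days 5, 7 and 14. They differ on 2, 3, 4, 6, 10, 21 and 28.
- Section 13 table and Table 1 differ on Day 28 only.

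**2. Match with viral load** (footnote 2 days, restricted to Days 1-14: 2, 4, 6, 7, 14)

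- Sparse days in the text that match: Day 7, so 1.
- Sparse days in the table that match: 2, 4, 6, 7 and 14, so 5.

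Under the text, the 12 intensive participants would also have Day 14.

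**3. Time since the last dose**

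The last nitazoxanide dose is at 8 pm on Day 14. A 12-hour sample counted from an 8 am clock time falls at 8 pm.

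- Day 21: 7 × 24 = 168 hours after the last dose.
- Day 28: 14 × 24 = 336 hours after the last dose.

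The protocol gives no half-life, so I assume a range of 1 to 24 hours. The fraction left is 2^(−t / half-life).

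| Assumed half-life | Fraction left on Day 28 |
|---|---|
| 1 to 6 h | effectively nil (about 1 × 10⁻¹⁷ at 6 h) |
| 12 h | 2^(−28) ≈ 4 × 10⁻⁹ |
| 24 h | 2^(−14) ≈ 0.006% |

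Section 13 itself reports no significant accumulation of the metabolites at 500 mg every 12 hours, so the upper end of this range is generous.

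**4. Specimens**

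- Sparse blood spots in the table: 49 × 6 = 294, of which 49 fall on Day 28 and 49 × 5 = 245 are on treatment.
- If the text were followed on Days 21 and 28: 49 × 2 = 98 off-treatment samples.
- Intensive blood spots: 12 × 7 × 2 = 168.

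**5. Atazanavir/ritonavir timing**

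- Sparse: 12 hours after 8 am is 8 pm, which is 24 hours after the previous evening's dose. This gives the trough only.
- Intensive: from 8 am + 0.5 h (12.5 hours after atazanavir/ritonavir) to 8 am + 12 h (24 hours after). This gives an approximate 12-hour level and the trough, in 12 participants.

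**The case against.** The best defence is that there is one real schedule. The Section 13 table and Table 1 agree on every treatment day, and the text defers to the table, so the text is a single stray sentence. The table's blood-spot days also equal all six post-baseline viral-load days. This largely stands. It limits the fault and makes the fix obvious, but it does not make the sentence correct, and it leaves the Day 28 entry without a dose.

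A reader might infer that the exposure-response aim is not served because every sparse sample is at 12 hours. The documents do not support that. Twelve participants have seven-point profiles on days 5 and 14, and up to 49 have on-treatment troughs on five days. Trough is also the exposure measure behind the dose rationale in Section 2.1 (Figure 2). What remains is a limitation: outside those 12, individual peak and total exposure are poorly informed.

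A reader might also conclude that PK cannot be paired with viral load, pointing to PK saliva on only three days. That confuses saliva as a PK specimen with the viral-load saliva to which footnote 3 refers. Under the table, the blood spots pair fully.

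On footnote 5, one can argue that the claim is joint and the intensive samples supply the 12-hour level. That is a possible reading, but the sentence names both kinds of sampling and only one of them delivers it. On footnote 3, the word for all patients probably contrasts with the 12 selected participants, and the table's n = 49 settles who is meant. The wording still needs correction.

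**Conclusion.** The contradiction is confirmed. The Section 13 text shares 2 of its 5 sparse days with its own table. The table and Table 1 disagree on Day 28 alone. Following the text would cut on-treatment sparse days that match viral load from five to one. Days 21 and 28 lie 7 and 14 days after the last dose, so a sample at 12 hours after a dose cannot be taken there. The Day 28 entry alone spends 49 blood spots for essentially no exposure information. Footnote 5 overstates what sparse sampling gives for atazanavir/ritonavir.

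These results rest on dosing from Day 1 to the evening of Day 14, on 8 pm samples being drawn before the 8 pm dose, and on the assumed half-life range. The matching counts use the viral-load days in footnote 2. Section 5 also names Day 10 for PCR negativity, although footnote 2 has no Day 10 sample. If one were added, the text would match on two days (7 and 10) and the table still on five.

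PK is not among the primary, secondary or safety outcomes in Section 5. The damage is confined to the PK and exposure-response work and does not reach the efficacy conclusions.

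**What to change.** - Put one sparse PK list in the Section 13 text, its table and Table 1: the on-treatment viral-load days already tabulated (2, 4, 6, 7, 14).
- Delete Days 3, 10, 21 and 28 from the sparse PK lists. If an off-treatment sample is wanted, state its purpose and a time reference other than a dose on that day.
- In Table 1 footnote 3, replace all patients with the intervention arm (n = 49), and limit the pairing to on-treatment viral-load days so that Days 0 and 28 are not drawn in.
- In footnote 5, say that sparse sampling gives the atazanavir/ritonavir trough and that an approximate 12-hour level comes from the intensive samples.

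The cost is a wording amendment, with the approvals that Section 15 requires. It saves 49 blood spots against the current table.

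Two further changes may look attractive but are not needed. Moving some sparse samples to just before 8 am would still give a tizoxanide trough, because that is again 12 hours after a nitazoxanide dose. Adding PK saliva on all five days would raise sparse specimens from 49 × 6 + 49 × 3 = 441 to 49 × 5 + 49 × 5 = 490.

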#### 14. Ethical Considerations

This trial will be conducted in compliance with the protocol, with the principles of ICH Guideline E6 for Good Clinical Practice, the Declaration of Helsinki, and all applicable regulatory requirements. Ethical clearance for the conduct of this trial has been obtained from the National Health Research Ethics Committee (NHREC), Abuja, Nigeria (approval number: NHREC/01/01/2007-26/08/2020) and the University of Liverpool's Health and Life Sciences Ethics Committee - human participants, tissues and databases (reference number: 8074). Clinical Trial Authorisation was granted by the National Agency for Food and Drug Administration and Control (NAFDAC) on 06/10/2020. Participation will be entirely voluntary and patients will be allowed to withdraw their consent at any stage. In addition, not consenting will not affect care in any way. All samples will be anonymised and retained until completely used up and no clinical data will be kept or passed on to a third party. No financial benefits will accrue to the researchers as a direct result of this study and samples may not be sold for profit, in cash or in kind.

#### 15. Protocol Amendment

The trial protocol has been designed to meet highest level of standard that will primarily ensure safety of participants and output of good and reliable data. However, major and minor modifications can sometimes be made to remove or avoid any unanticipated risk or harm to the participant or affect the integrity of study outcomes. Whenever this happens, the amendments will be saved in a new version of the protocol, with the changes from previous version highlighted in the version history page. The amended protocol will be shared with all investigators. The revised and previously approved versions of the protocol will be submitted to the ethics committees (NHREC, Nigeria and the University of Liverpool Health and Life Sciences) and NAFDAC for approval before the changes are implemented in the trial.

 Both intensive and sparse PK sampling will be performed after the morning dose of 1000 mg nitazoxanide. This will also capture the C12 and Ctrough of atazanavir/ritonavir which will be taken with the evening dose of 1000 mg nitazoxanide.

